#### 6.4 Prior and Concomitant Therapy; Prohibited Medications

All medications during the entire study period should be recorded. All drug therapies for AS should be stable prior to the first Golimumab administration (as stated in the inclusion/exclusion criteria). Changes in concomitant therapy required for the treatment of

adverse events are allowed. All changes in the concomitant therapy must be recorded. Allowed changes in the AS therapy are described in the section 6.5.2 “Rescue Treatments”.

The following medications are prohibited during the study:

- Systemic steroids in a dose >10 mg (prednisolone equivalent) per day,
- DMARDs other than methotrexate or sulfasalazine,
- Biologics other than the study drug Golimumab,
- Any investigational drugs of chemical or biological nature,
- Live vaccines (during the study and 60 days after the last drug administration).

## 6.5 Study Treatment

### 6.5.1 Treatments Administered

Included patients will receive Golimumab 50 mg administered subcutaneously by the study personnel or self-administered during the study visit at baseline (week 0), Week 4, 8 and 12. The following dosages will be self-administered by the patient as SC injections every 4 weeks. In the Phase II, subjects included in the Golimumab-Combined-Arm will receive in addition Celecoxib 400mg per os (2 capsules containing 200 mg each) daily.

If the administration of the study drug Golimumab should not be performed in the opinion of the investigator at the planned date due to AE (e.g. infections or clinically significant laboratory abnormalities), the administration should be possible after resolution of the AE, but not later than 14 days after the scheduled injection date. If Golimumab administration is not possible within this time window, this injection should be skipped and next injection has to be done according to the original schedule. Treatment with Celecoxib could be interrupted if necessary for up to 4 weeks.

### 6.5.2 Rescue Treatments

Only Golimumab responders will be included in the phase II of the trial, therefore substantial problems with insufficient efficacy of treatment or non-compliance during this phase are not expected. Nonetheless, there will be the possibility of rescue treatment for all patients experiencing pain and stiffness:

- 1) Analgesics without anti-inflammatory capacity (e.g. paracetamol, metamizole or tramadol) in usual therapeutic doses, which will be prescribed by the rheumatologist.

- 2) For patients in the Golimumab-monotherapy-arm and insufficient response to analgesics, on-demand use of NSAIDs up to 50% of the maximum therapeutic dose (i.e. Ibuprofen up to 1200 mg/d; see table below) will be allowed; but, under no circumstance Celecoxib should be taken in the control group.

In both arms of the phase II a proton pump inhibitor (PPI) in standard dose could be prescribed by the rheumatologist as needed, reflecting standard of care for treatment or prevention of gastric side effects of NSAID.

**Table.** Approved maximal daily doses of the most common NSAIDs in Germany.

| NSAID        | Approved maximal daily dosage in Europe (Germany), normally for arthritis | Label for AS in Europe (Germany) |
|--------------|---------------------------------------------------------------------------|----------------------------------|
| Ibuprofen    | 2400 mg
(1-3 divided doses)                                            | Yes                              |
| Indomethacin | 150 mg
(1-3 divided doses)                                             | Yes                              |
| Ketoprofen   | 200 mg
(1-2 divided doses)                                             | Yes                              |
| Naproxen     | 1000 mg
(1-2 divided doses)                                            | Yes                              |
| Piroxicam    | 20 mg
(1-2 divided doses)                                              | Yes                              |
| Meloxicam    | 15 mg
(once daily)                                                     | Yes                              |
| Diclofenac   | 150 mg
(1 single or 2-3 divided doses)                                 | Yes                              |
| Aceclofenac  | 200 mg
(1-2 divided doses)                                             | Yes                              |
| Etoricoxib   | 90 mg
(1 single dose)                                                  | Yes                              |

### 6.5.3 Drug supplies, Packaging and Labelling

MSD Sharp & Dohme GmbH (Haar/Germany) will provide the TNF-blocker (Golimumab) as an open-label supply in carton boxes (Simponi®). Each carton box will contain one pre-filled syringe with Golimumab 50mg / 0.5 ml. On the product label, the study identifier, the product identity and strength, batch number, directions for use, list of excipients, storage conditions and expiration date will be indicated.

Celecoxib (Celebrex® manufactured by Pfizer Deutschland GmbH) will be provided as an open-label supply in carton boxes containing 100 capsules á 200mg. On the product label, all details will be indicated too.

#### **6.5.4 Storage, Disposition and Drug Accountability**

Golimumab pre-filled syringes must be stored locked in a secure place, protected from light at 2° to 8°C. Study medication must not be frozen at any time. A storage temperature log is to be maintained on a daily basis. In case of temperature regimen deviations the drug should be quarantined and not dispensed until Sponsor deems the medication as acceptable.

Celecoxib capsules are to be stored at room temperature, no temperature log is needed.

The investigator or designee should verify that study drug supply is received intact at the appropriate temperature and in the correct amount. For regulatory requirements (GCP), the site has to maintain 1.) a “Site Drug Accountability Log”, which includes information on the date of receipt, box count, the batch number, date dispensed, subject number and identification of the person who dispensed the drug and 2.) an individual “Patient Drug Accountability Log” including information on date and box count of dispensed and count of received (empty/used) syringes or pill blisters. The investigator is responsible for accounting of the used and unused study drug. Expired study drug must not be administered.

All returned study medication (e.g. empty syringes, broken pill containers/blisters) will be collected, documented and disposed by the study site. At every study visit complete new boxes / containers of study medication will be handed to the patient.

The study drug must not be used for other reasons than the current study and only in patients who were enrolled in the study and gave a written informed consent. Celecoxib from this study is only to be handed to patients randomized into the combination arm of the Phase II, but not as rescue medication for patients in the Golimumab only arm.

#### **6.5.5 Treatment Compliance**

The subject him/herself or the qualified study staff will administer all injections of study drug. In order to document compliance with the treatment, administration (dates and times) of the study drug will be recorded in the patient’s chart and in the Drug Accountability log. Subjects will be instructed to return all drug containers / syringes from Golimumab and blisters from Celecoxib (even empty) to the study site.

## 6.6 Study Discontinuation

### 6.6.1 Discontinuation of Individual Subjects

A subject may withdraw from the study at any time. The investigator may discontinue the subject participation due to adverse events, safety concerns or subject's failure to comply with the protocol.

Subjects will be withdrawn from the study if one of the following occurs:

- The subject requests withdrawal from the study.
- The subject does not achieve a good clinical response (improvement of at least  $\geq 2$  absolute points on a 0-10 scale of BASDAI after 12 weeks of treatment with Golimumab in the phase I.
- The female subject of child-bearing potential does not perform effective contraceptive methods or becomes pregnant during the study.
- The subject is diagnosed with a malignancy or lymphoproliferative disorder.
- The subject develops allergic reaction to / intolerance of the study drug.
- The subject is diagnosed with multiple sclerosis or demyelinating disease.
- The subject develops a lupus like syndrome.
- Two consecutive Golimumab injections were not performed.
- For patients in the combination arm: Study treatment with Celecoxib was interrupted for more than 4 weeks.
- Introduction of a prohibited medication after the subject started the study drug, when continuation of the study therapy would place the subject at risk as defined by the investigator.
- The subject receives a live vaccine during the study period.
- Major surgical intervention during the study period.
- The subject is diagnosed with active tuberculosis, opportunistic infection or any other severe infection including acute Hepatitis B or HIV.
- Subject is non-compliant with anti-tuberculous treatment (if this medication is required).

- Any AEs, including clinically significant laboratory abnormalities, when continuation of the study therapy would place the subject at risk as defined by the investigator.
- Any other reason at the investigators discretion to ensure the well-being of the subject.

In case of premature discontinuation of the study procedures outlined in the assessment schedule for the “Early Termination Visit” should be performed within 4 weeks after last dose of study drug. The reason for the discontinuation must be documented. After study discontinuation the patients will be treated according to available standards of care.

### 6.6.2 Discontinuation of the Entire Study

Both the sponsor and the investigator reserve the right to terminate the study at any time. In this case, both parties will arrange the procedures on an individual study basis after review and consultation. Advance notice is not required by either party if the study is stopped due to safety reasons.

Criteria for discontinuation of the entire study:

- Negative benefit/risk assessment due to new information
- Decision of the ethical committee or of the federal authority
- Certain circumstances, such as lack of drug supply from the third parties, making continuation of the study impossible.

When terminating the study, the investigator will assure that adequate consideration is given to the protection of the patient’s interests. In case of premature termination of the study all collected data has to be analysed and a report has to be written. The sponsor (Charité) has the responsibility by law (AMG / GCP) to inform the federal regulatory authority, the ethics committees and other possibly related authorities within 15 days, giving detailed reason for the premature termination.

## 6.7 Study Procedures

The study procedures are outlined in the assessment schedule. All procedures will be documented in the patient’s charts and in the patient’s case report form (CRF).

### *Informed Consent*

An Independent Ethics Committee (IEC) / Institutional Review Board (IRB) approved informed consent will be reviewed, signed and dated by the subject, before any study-related procedures are undertaken.

### *Inclusion/Exclusion criteria*

Subjects should meet all inclusion and none of the exclusion criteria at both screening and Baseline Visits in order to be eligible for the study.

### *Demographics*

Patient's age and gender will be collected at the Screening Visit.

### *Medical/Surgical history*

A complete medical and surgical history including history of articular (inflammatory back pain, peripheral arthritis, enthesitis, dactylitis) and extraarticular manifestations (uveitis, psoriasis, inflammatory bowel disease), and spondyloarthritis (SpA) family history will be collected during the Screening Visit and updated at Baseline Visit and throughout the study as applicable. Smoking status will be collected at different time points. The certificate of vaccination ("Impfausweis") of the patient shall be checked at screening visit, recommended vaccinations according to local guidelines should be performed prior to Baseline; in case of live vaccines (e.g. measles, rubella, varicella) start of golimumab shall not be prior to 12 weeks after vaccination (see Exclusion Criterion 29).

### *Prior medication for SpA*

As part of in-/exclusion criteria.

### *Concomitant medication*

All concomitant medications will be collected at screening and updated during following visits.

### *Vital signs, weight, height*

Vital signs including heart rate, blood pressure (both measured in sitting position after resting for at least 5 minutes), weight and height will be obtained as outlined in the assessment schedule.

### *Physical examination*

A routine physical examination will be performed as outlined in the assessment schedule.

*Axial mobility measurement*

Axial mobility measurements will include BASMI  and chest expansion measurement  and will be performed as outlined in the assessment schedule.

*Laboratory analyses*

Blood chemistry, haematology, C-reactive protein, erythrocyte sedimentation rate, serum pregnancy test (female subjects), hepatitis B (HBs-Ag and anti-HBc) serology, and urinalysis will be performed as outlined in the assessment at the respective local laboratory of the study site as a part of clinical routine in patients treated with TNF blockers. At screening, blood analysis includes also Quick-Test, International Normalized Ratio (INR) and activated Partial Thromboplastin Time (aPTT) to recognize patients with high bleeding risk.

In patients with positivity in the above mentioned tests for hepatitis B, further recommendations exist: due to small risk (1.7-5%) for HBV reactivation in “HBs Ag negative & anti HBc positive” patients, a participation of the patient in the CONSUL study is possible only after hepatologist assessment (see Table 1).

Table 1. How to proceed with positive Hepatitis B virus tests

| HBs Antigene | Anti HBc Antibodies | Recommendation                                                                                                                                                                                                               |
|--------------|---------------------|------------------------------------------------------------------------------------------------------------------------------------------------------------------------------------------------------------------------------|
| negative     | Negative            | Study participation possible                                                                                                                                                                                                 |
| Positive     | pos./neg.           | Exclusion criterion in CONSUL, general recommendation for referral to a hepatologist                                                                                                                                         |
| Negative     | Positive            | Referral to hepatologist:
Testing for HB virus load (PCR):
-negative – study participation possible, “watchful waiting”
-positive – anti TNF therapy might be discussed after initiation of pre-emptive HBV therapy |

Analyses for research purposes (blood tests for biomarkers of inflammation, bone / cartilage turnover, stool microbiome) will be performed centrally at the Charité Berlin and corresponding laboratories.

*Tuberculosis screening*

All patients will undergo an IGRA tuberculosis serum test (QuantiFERON®-TB Gold In-Tube test or T.SPOT TB®) and a chest x-ray (tests performed within three months prior to screening can be accepted) at Screening Visit. The history of active or latent tuberculosis infection as well as physical examination will be collected in order to reveal signs and

symptoms suggestive for tuberculosis. Patients with clinical or radiological signs suggestive for tuberculosis will be excluded from the study participation. Subjects with a negative tuberculosis serum test are eligible to continue with the screening procedures.

In case of a positive tuberculosis serum test but no radiological or clinical signs suggestive for tuberculosis the subject might participate in the study upon initiation of the prophylactic anti-tuberculous treatment (e.g., isoniazid 300 mg daily initiated 4 weeks prior to the first administration of Golimumab and continued for a total of 9 months in combination with pyridoxine).

### *Electrocardiography (ECG)*

A 12-lead ECG should be performed in all patients, who are considered by the investigator to be at risk of having unrecognized cardiovascular pathology (coronary heart disease, rhythm and conduction disturbances).

### *Patient questionnaires*

Patients questionnaires (BASDAI, BASFI, Patient's Global, overall pain, nocturnal pain, ASAS Health Index, Patient Acceptable Symptom State PASS) represent validated tools for the assessment of disease activity, functional status, quality of life and overall well-being in AS; they will be completed according to the assessment schedule.

### *Physician's Global and Physician Acceptable Symptom State*

Represent global assessment of disease activity and patient's symptom state by the investigator will be performed according to the assessment schedule.

### *X-rays of the spine*

X-rays of the lumbar and cervical spine (lateral views) will be performed during screening only if there were no image performed within the previous 24 months. Those images are central for the conduct of the study (primary outcome; inclusion criterion #5b and exclusion criterion #10). Quality of the x-rays should allow this assessment, i.e., images should be available in electronic form or as x-ray film (no paper printouts). If no images fulfilling these criteria are available, X-rays of the cervical and lumbar spine should be performed during the screening period. A second set of X-rays of lateral cervical and lumbar spine must be performed at Week 108, or in case of an early termination (ET) if the patient reached at least Week 84..

### *Magnetic resonance imaging (MRI) of spine and sacroiliac joints*

MRI of the spine and sacroiliac joints will be performed during screening (before first injection of Golimumab), and at Week 108 (or in case of an early termination (ET) if the patient reached at least Week 84) ) in a sub-study with patients of study sites in Berlin & Brandenburg having no contraindication for this investigation. No contrast agents will be applied.

#### *Golimumab administration*

Golimumab 50 mg will be administered subcutaneously by the qualified study personnel or self-administered by the subject during the study visits at baseline and then every 4 weeks until Week 108 – last injection will be at week 104 (for non-responders dropping out of study at week 12 – last injection at week 8).

## 7 SAFETY CONSIDERATIONS

### 7.1 Definition and Reporting of Adverse Events

An adverse event (AE) is defined as any new undesirable medical occurrence in a clinical investigation subject / patient having received at least one dose of a study drug; this does not necessarily have to be a causal relationship with the study treatment. An AE can therefore be any unfavourable and unintended sign (including an abnormal laboratory finding, for example), symptom, or disease during the time course of the study.

Such an event can result from use of the drug as stipulated in the trial or labelling, as well as from accidental or intentional overdose, drug abuse, or drug withdrawal. Any worsening of a pre-existing condition or illness is considered an AE. Worsening in severity of a reported AE should be registered as a new AE. Laboratory abnormalities and changes in vital signs are considered to be AE only if they result in discontinuation from the study, needs therapeutic medical intervention and/or if the investigator considers them to be an AE.

Following the subject's written consent to participate in the study, all serious AEs (SAE) should be collected. All other AEs should be collected throughout the treatment period from Week 0 until Week 108 and 4 weeks thereafter in the "Safety-Follow-up Visit" at Week 112.

If AEs occur, the subject should be followed until resolution or stabilization, and reported as serious AEs if the AE becomes serious. This also applies to subjects experiencing AEs that cause interruption or discontinuation of the investigational product, or those experiencing AEs that are present at the end of their participation in the study; such subjects should receive post-treatment follow-up as appropriate. If an on-going AE changes in its severity or in its perceived relationship to study drug, a new AE entry for the event should be completed.

A pre-planned elective surgery/procedure scheduled to occur during the study will not be considered an AE if the surgery/procedure is being performed for a pre-existing condition and no worsening of the pre-existing condition occurred during the study.

All identified AEs must be recorded and described on the appropriate AE section of the CRF. If known, the diagnosis of the underlying illness or disorder should be recorded, instead of the individual symptoms. The following information should be captured for all AEs: date of onset and resolution, severity of the event (see definitions), investigator's opinion of the relationship to investigational product (see definitions), treatment required for the AE, cause of the event (if known), and information regarding resolution/outcome. The following categories and definitions of severity should be used:

- Mild (Grade I) - awareness of event but easily tolerated.
- Moderate (Grade II) - discomfort enough to cause some interference with usual activity.
- Severe (Grade III) - inability to carry out usual activity.
- Very severe (Grade IV) - debilitating significantly incapacitates subject despite symptomatic therapy.

The following categories and definitions of causal relationship to study drug should be used:

- No related: there is no causal relationship (in the opinion of the investigator) between the AE and use of the study drug.
- Doubtful: there are other factors such as concomitant disease, medications or the relationship in time, suggesting that a causal relationship is unlikely.
- Possible: the AE might be due to the use of the drug. Other factors such as concomitant drug or disease are inconclusive. The relationship in time is reasonable; therefor, the causal relationship cannot be excluded.
- Probable: there is a reasonable causal and temporal relationship between the study drug and the AE. Other reasons are less likely.
- Very likely: there is a reasonable causal and temporal relationship between the study drug and the AE. The AE is described as a side effect of the study drug and cannot be reasonably explained by an alternative explanation. The relationship in time is very suggestive (e.g. it is confirmed by dechallenge and rechallenge).

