| Study phase:                                           | IV                                                                                                                                                                                                                                                                                                                                                                                                                                                                                                                                                                                                                                                                                                                                                |
| Study design:                                          | Randomized, controlled, open-label multicenter study                                                                                                                                                                                                                                                                                                                                                                                                                                                                                                                                                                                                                                                                                              |
| Indication:                                            | Ankylosing spondylitis (AS)                                                                                                                                                                                                                                                                                                                                                                                                                                                                                                                                                                                                                                                                                                                       |

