|                 | 
n=190; assuming a 10% screening failure rate approximately.
 
To be allocated to trial:
n=170 patients with active AS despite treatment with NSAIDs alone will be included in the phase I of the trial and treated with Golimumab. Only patients with good clinical response after 12 weeks of treatment will be enrolled in the phase II of the trial. It is assumed that approximately 60% (n=100) of patients included in phase I will continue in the phase II of the study, considering that elevated CRP at baseline is currently the best response predictor for TNF-blocker therapy.
 
To be analysed:
n=100 (n=50 in each group) patients will enter phase II of the trial (intention-to-treat population - ITT) after 1:1 randomization.
 
Statistical analysis:
 
Efficacy:
Efficacy of the therapy in reduction of radiographic spinal progression will be assessed by the modified Stoke Ankylosing Spondylitis Spine Score (mSASSS). mSASSS is a radiographic score measuring structural changes in the lumbar and cervical spine. Images will be scored by 2 trained readers in a blinded manner that allows the open-label (although randomized) design of the trial.
The primary efficacy endpoint will be radiographic spinal progression assessed by the change in the mSASSS score over two years of therapy in both groups. The primary analysis will be based on the intention-to-treat population, a secondary one in patients with complete sets of radiographs at two time points. A two-sided Mann-Whitney U-test will be applied to compare the mSASSS progression between both treatment groups in both analyses.
 
Safety:
Safety outcome will include absolute number and percentage of patients who experienced adverse events (AE), serious AE, AE of interest (infections, malignancies, gastrointestinal events: ulceration, bleeding, perforation, gastric outlet obstruction; thrombotic cardiovascular events: myocardial infarction, stroke, pulmonary artery embolism, peripheral arterial of venous thrombosis; renal and hepatic function deterioration), as well as a proportion of patients who discontinued the study because of AEs.
In order to address possible long-term safety issues related to long term use of NSAIDs a safety Follow-Up Visit will be performed 3 months after discontinuation of the study treatment (either week 108 or the last study visit in the case of early discontinuation).
Safety population will include each patient who received at least one dose of Golimumab with or without Celecoxib. Statistical comparisons will be based on event rates per 100 patient years of exposure. Rates will be compared by exact Poisson methods.
 
Secondary endpoint(s):
Mann-Whitney U-test, linear mixed models, and Chi-square test will be used in order to evaluate differences in the secondary outcome parameters between treatment groups.
 |

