### Safety

- Number of AE and percentage of patients experienced AE, serious AE and events of interest: infections, malignancies, gastrointestinal events (ulceration, bleeding, perforation, gastric outlet obstruction), thrombotic cardiovascular events (myocardial infarction, stroke, pulmonary artery embolism, peripheral arterial or venous thrombosis), renal impairment (creatinine > 1.8 mg/dl or increase > 0.5 mg/dl vs. Baseline) and hepatic deterioration (AST, ALT, AP or GGT > 5-fold ULN). A safety follow-up visit will be performed 3 months after the discontinuation of the study treatment (either at Week 108 or last study visit in case of early discontinuation) in order to address possible long-term safety issues with special regard to continuous use of NSAIDs.

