### 13.6 Safety Data Analysis

Safety data will be analysed describing frequency and types of adverse events. All adverse events will be coded and tabulated by body system and preferred term for individual events within each body system, and will be presented in descending frequency. Adverse events will also be tabulated by severity and relationship to the study medication. Serious adverse events will be summarized separately.

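### Section 7.1 registers worsening of an AE as a new AE and asks for further entries on re-rating, with no link between entries of one event, while AE numbers and Poisson-compared rates are event-based

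*Protocol*

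**What the plan says.** Section 7.1 contains two instructions on an AE that changes. The first is "Worsening in severity of a reported AE should be registered as a new AE". The second, at the end of the paragraph on follow-up of AEs, says that, when "an on-going AE changes in its severity or in its perceived relationship to study drug, a new AE entry for the event should be" filled in.

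Section 7.1 also lists what to capture for every AE: onset and resolution dates, severity, relationship, treatment, cause and outcome. A reference to an earlier entry for the same event is not on that list.

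Three places use these records:

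- Section 5.2, Safety, has as endpoint "Number of AE and percentage of patients experienced AE, serious AE and events of interest".
- The synopsis, under statistical analysis of safety, says "Statistical comparisons will be based on event rates per 100 patient years of exposure" and "Rates will be compared by exact Poisson methods".
- Section 13.6 says "Adverse events will also be tabulated by severity and relationship to the study medication".

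The synopsis describes the trial as "Randomized, controlled, open-label multicenter study".

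**The concern.** The number of AEs and the rate per 100 patient-years both depend on what counts as one event. Under section 7.1 an AE that starts mild and becomes moderate is two AEs. If it later improves, or the investigator revises the causality, the second sentence produces another entry. Its status is unclear, because it could be a separate AE or a continuation record of the same one.

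Two things are at stake. First, an exact Poisson comparison treats each count as an independent occurrence. Two records of one event in one patient are not independent, so the counts vary more than the test allows for. This holds even when both arms are recorded in the same way. Second, sites know the allocation. If they re-rated events more often in one arm, the rate ratio would shift with no difference in harm.

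Section 4.3.3 says that any benefit must be weighed against the possible risks of continuous NSAID therapy. The rate comparison is the only formal statistical comparison of safety that the protocol names.

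**Working it through.** The protocol gives no AE rate and no power statement for safety, so there is no stated figure to reproduce. The calculation below is an illustration under labelled assumptions.

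**Inputs from the protocol**
- 50 patients per arm in phase II (synopsis).
- 96 weeks of randomized treatment (section 13).
- Two-sided 0.05 (section 13.5).
- Exact Poisson comparison of rates (synopsis).

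Exposure per arm without dropout is 50 × 96 / 52 = 92.3 patient-years.

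**Assumptions not in the protocol**
- The true AE rate is the same in both arms, from 50 to 300 per 100 patient-years.
- A share q of events gives one extra entry. A variant lets the number of extra entries per event be Poisson with mean q.

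**Step 1: equal re-entry in both arms.** With at most one extra entry per event, an event contributes 1 or 2 counts. Its mean is 1 + q and its mean square is (1 − q) + 4q = 1 + 3q. If events are Poisson, the variance of the total divided by its mean is

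(1 + 3q) / (1 + q).

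At q = 0.2 this is 1.6 / 1.2 = 1.33, where the Poisson test assumes 1. A normal test at the nominal 5% would then reject with probability 2 × [1 − Φ(1.96 / √1.33)] = 2 × [1 − Φ(1.70)], or about 9%. The exact test is conservative on discrete counts, so its rate is slightly lower.

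Simulation of the exact conditional (binomial) test, 40,000 runs per setting, gives these rejection rates with no true difference:

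| Extra entries per event, both arms | Rejection | Rate ratio |
|---|---|---|
| 0 | about 4% to 5% | 1.00 |
| 0.2 | about 8% to 9% | 1.00 |
| 0.5 (Poisson variant) | 13% to 14% | 1.00 |
| 1.0 (Poisson variant) | 20% to 21% | 1.00 |

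These figures hardly depend on the assumed AE rate.

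**Step 2: unequal re-entry (hypothetical).** With equal true rates, the expected rate ratio is (1 + q in the combination arm) / (1 + q in the control arm).

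| Control / combination | Rate ratio | Rejection at 100 to 200 AEs per 100 patient-years |
|---|---|---|
| 10% / 20% | 1.2 / 1.1 = 1.09 | about 11% to 17% |
| 10% / 30% | 1.3 / 1.1 = 1.18 | about 25% to 42% |

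Over 50 to 300 AEs per 100 patient-years, the 10% / 30% case runs from about 16% to 55%. Unlike step 1, this result depends strongly on the AE rate and on the assumed difference in re-entry.

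**Step 3: one count per event.** Setting the extra entries to zero restores a rate ratio of 1.00 and rejection of about 4% to 5%.

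**The case against.** The strongest reply is that section 7.1 is a recording rule. Its second sentence speaks of a new entry for the event, which keeps the event singular. Collapsing entries at the worst grade is ordinary content for a statistical analysis plan, and section 13.3 refers to a separate plan. Much of this stands for the second sentence. A reader might infer that every improvement and every revised causality becomes an additional AE in the analysis, but the wording does not go that far. The reply does not cover the first sentence, which makes worsening a new AE. Nor can a later plan reliably merge records if their link was never captured. It would have to guess from terms and dates.

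A reader might also infer that the combination arm will look worse, because only that arm receives celecoxib and the trial is open-label. The documents do not support this. Both arms receive golimumab, so relationship to study drug can be reconsidered in either. Control patients may take rescue NSAIDs. No passage gives a re-entry rate, let alone one per arm. The ratio of 1.18 is a direct result of the chosen inputs.

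Three further limits stand:

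- The percentages of patients with an AE or a serious AE, and the proportion discontinuing because of AEs, count patients and cannot be changed by splitting.
- The events of interest that bear most on NSAID risk are mostly discrete (perforation, infarction, stroke) or defined by laboratory thresholds, so repeat grading affects them little.
- The simulation covers only the randomized period without dropout, whereas the safety population starts from the first golimumab dose and section 13.8 expects dropout below 20%.

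The excess rejection in step 1 could also be described as overdispersion under a Poisson test. That is correct, but here the recording rule creates the overdispersion, and counting each event once removes this source of it.

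**Conclusion.** The point holds in a limited form. As written, each worsening adds to the AE number and to the event rate. Entries made for improvement or revised causality may add more, because the protocol leaves their status open and provides no link between entries. With equal recording in both arms, the rate ratio is unbiased but the test is too liberal: about 8% rejection instead of about 4% at an assumed 20% re-entry, and more if re-entry is more frequent. Bias in the ratio arises only if re-entry differs between arms. That is a possibility of the open-label design and not something the protocol shows.

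The effect is confined to AE numbers, AE rates and the tabulation by severity and relationship, where one event can appear in several cells. It does not undermine the patient-level safety results. A correction is worth making because it is cheap, and because a link between entries is hard to reconstruct after data collection.

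**What to change.** 1. Reconcile the two sentences in section 7.1 so that one rule governs worsening, improvement and revised causality.
2. Keep the dated changes in severity and causality, but tie each to the original AE by an event identifier in the eCRF.
3. State in section 5.2 and the synopsis that AE numbers and rates count each linked event once, at its maximum severity and with a prespecified causality, such as the strongest relationship recorded. Apply the same convention to the tables in section 13.6.

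The cost is an amendment of a few sentences, one eCRF field and slightly more data-management work. Reported AE counts will be lower than under the present wording. No severity or causality history is lost.
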